### aPRP collection

aPRP will be collected from a large-bore central venous access via gravity drainage, with approximately 15–20 mL/kg whole blood collected prior to heparin administration. The collected whole blood will be divided into aPRP and red blood cells using an autologous transfusion system (Sorin Electa Essential; Sorin, Italy). The target yield of aPRP is 10 mL/kg. The amount of PRP collected can be determined using kilogram mass, and most research [2, 11] specify a collection of 10 mL/kg of aPRP, with the exception of the 1994 study [12], which collected 15 mL/kg of aPRP.

Specific steps: An anticoagulation prefilled blood collection tube is connected to an external central venous access for blood collection. The anticoagulant solution is maintained at a constant drop to mix with the blood in the tube, and the blood entering the centrifuge chamber is centrifuged to separate aPRP and RBCs. While the blood is being drained, a crystalloid solution is infused through the peripheral vein to maintain hemodynamic stability. Blood collection was stopped when the target volume was reached. All blood collection, extraction and other operations required strict asepsis, and the resulting aPRP was stored inter-operatively at room temperature under shaking conditions. The whole separation and extraction process is completed before CPB heparinization. The aPRP will then be stored in sodium citrate collection bags at room temperature (usually 22~24 °C). When extracorporeal circulation is stopped, collected whole blood is inserted in a blood bag containing sodium citrate and transfused, heparin is neutralized with ichthyoglobulin, and no active bleeding is detected throughout operation. The anesthesiologist decided to perform aPRP.

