**Methods and analysis:**

This is a prospective, single-center, double-blind controlled clinical trial including 160 patients randomized 1:1 to receive aPRP (test group) or autologous whole blood (ANH, control group). The primary objective is to compare the drainage volumes in the two groups at 24, 48, and 72 h postoperatively. Secondary outcomes include input of allogeneic blood and blood products and durations of aortic block, extracorporeal circulation, deep hypothermic arrest of circulation, tracheal extubation, hospital stay, requirement for secondary surgical hemostasis, and application of intra-aortic balloon pump or extracorporeal membrane oxygenation in the two groups. In addition, heart rate, systolic blood pressure, diastolic blood pressure, central venous pressure, and thromboelastography recorded before blood reservation (T1), after blood reservation (T2), before blood transfusion (T3), and after the blood is returned (T4) to the transfusion will be compared between the two groups of patients.

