#### Double-blind randomization and allocation concealment

Enrolled patients undergoing aortic surgery will be divided randomly into a control group (ANH) and an aPRP group using a computer-generated sequence. Groups will be chosen before patient admission, and all patients and staff will be oblivious to their group assignment. The anesthesiologist will not be informed of the patient assignments, which are recorded and sealed in sequentially numbered opaque envelopes. Nurse anesthetists can give sealed envelopes and tell to prepare the items for the experiment based on group allocations; there are no differences in the look of the two sets of envelopes. The group assignment will be withheld from all patients and anesthesiologists. Following anesthesia induction, the anesthesiologist may perform the various surgeries in accordance with the coded number. Another anesthesiologist will document intraoperative data and followed up on the patient’s discharge. Finally, the data will be analyzed by a professional statistician.

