## Interventions

### General anesthesia

All patients will receive general anesthesia as follows: induction with midazolam 0.05 mg/kg, etomidate 0.3 mg/kg, sufentanil 0.5 μg/kg, and cis-atracurium 0.2 mg/kg. The anesthesia machine is connected after tracheal intubation, with the tidal volume set at 6–8 mL/kg and the respiratory rate at 12 breaths/min. The intraoperative end-tidal CO_2_ pressure is maintained at 35–45 mmHg by adjusting the respiratory parameters. Anesthesia is maintained with continuous pumping of 4–8 mg/kg/h propofol, with sufentanil and cis-atracurium injections at regular intervals. After induction of anesthesia, a large-diameter catheter is placed in the patient’s right internal jugular vein. The red blood cells were reinfused back into the patient after collection, and the collected aPRP was infused back into the patient after extracorporeal circulation following neutralization of heparin with fisetin.

There is no universally accepted criterion for determining the ideal amount of whole blood to collect for ANH, which is sometimes established clinically by diluting the target hematocrit or blood volume. However, according to the 2019 expert agreement on the clinical treatment of autologous blood transfusion, the total volume for blood collection should be as follows: 10–15% of total blood volume, with an increase to 20–30% of total blood volume in rare instances or in patients with improved health status. Accordingly, autologous blood is taken from the internal jugular vein following anesthesia and central venous cannulation with a volume of 8–10 ml/kg and Hct > 30% before CPB in the ANH group, and acute isovolumic hemodilution with sodium acetate-Ringer solution is conducted. If the collected blood is required for extracorporeal circulation reasons, this test will exclude this case. Ringer’s acetate will be used as a volumetric substitute to maintain hemodynamic stability throughout the blood collection process at a ratio of 1:1.5 (volume replenishment). Previous studies used crystalloids at a ratio of 1:3, and a pre-study test demonstrated that a ratio of 1:1.5 provided safe and effective volume replacement. At the end of the procedure, the patient is returned to the cardiac surgical care unit with assisted ventilation with a respiratory ball.

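### The two passages on returning the autologous product disagree on agent name, order, product and the role of bleeding or anesthesiologist decision, so return is not fixed identically for both arms

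*Protocol article*

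**What the plan says.** Two subsections under Interventions in the Protocol article deal with return.

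- General anesthesia: "the collected aPRP was infused back into the patient after extracorporeal circulation following neutralization of heparin with fisetin". It attaches no condition about bleeding. It describes how ANH blood is collected but not when it is returned relative to heparin neutralisation.
- aPRP collection: "When extracorporeal circulation is stopped, collected whole blood is inserted in a blood bag containing sodium citrate and transfused", followed by "heparin is neutralized with ichthyoglobulin, and no active bleeding is detected throughout operation. The anesthesiologist decided to perform aPRP". Earlier in the same subsection: "The collected whole blood will be divided into aPRP and red blood cells".

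Three other places bear on the point.

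- Double-blind randomization and allocation concealment: "The anesthesiologist will not be informed of the patient assignments".
- The Abstract anchors the last two measurement times to return: "before blood transfusion (T3), and after the blood is returned (T4". Data collection and management likewise places TEG before and after the return infusion. Study design {8} labels T3 and T4 with the reserving term instead.
- Data collection and management bases the use of fibrinogen, prothrombin complex, coagulation factors and platelets on the TEG results.

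**The concern.** Return of the stored product is the randomised intervention. A reader who wants to know what each arm receives, and when relative to heparin neutralisation, gets two answers for aPRP and no clear answer for ANH. The only sentence that places return of whole blood near neutralisation sits in the subsection on the other arm's product.

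Two things are at stake. First, T3 and T4 bracket the return. If return fell on different sides of neutralisation in the two arms, the T3-to-T4 change in TEG would include heparin reversal in one arm only. Because TEG also guides blood-product use, the difference could carry over into allogeneic product volumes, which Study design {8} names among the main objectives. Second, if giving aPRP depends on a decision with no stated criterion, receipt in the test arm is not fixed by randomisation. The section on non-adherence and missing data {20c} allows clear protocol violators to be left out of the final results, so a patient whose product was not returned could also leave the analysis.

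**Working it through.** The check is a comparison of text, so the two subsections are set side by side.

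| Item | General anesthesia | aPRP collection |
|---|---|---|
| Product returned | aPRP | whole blood, although in this arm it has been separated |
| Neutralising agent | fisetin | ichthyoglobulin |
| Position of neutralisation | before return | listed after transfusion |
| Absence of active bleeding | not mentioned | listed, with no conditional word |
| Role of the anesthesiologist | not mentioned | decides on aPRP, no criterion given |

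The sentences in aPRP collection can be read in three ways.

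1. As a time sequence in which whole blood means the ANH product. ANH blood is transfused, heparin is then neutralised, and aPRP is decided on afterwards. For aPRP this agrees with General anesthesia, but the arms are then on different sides of neutralisation. Bleeding is noted but not made a condition.
2. As a list of circumstances that must hold before aPRP is used. Clause order then carries no timing and the order conflict for aPRP disappears, but bleeding status and the anesthesiologist's decision now bear on whether the randomised product is given.
3. As a slip in which whole blood should read aPRP. The listed order then contradicts General anesthesia for aPRP itself, and ANH has no return rule at all.

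No reading makes the two subsections agree fully, and each leaves something open about when or whether a product is returned. Timing is the main problem under readings 1 and 3, and the role of bleeding under reading 2, so these should not be added together as if both were established.

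The documents give no share of patients whose product is not returned. To show only how sensitive the primary comparison would be, take the inputs in Determination of sample size: 316 ± 102 mL and 378 ± 133 mL, 80 per group, 80% power, 5% type I error (taken as two-sided).

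- Difference: 378 − 316 = 62 mL. SD: √((102² + 133²)/2) = 118.5 mL.
- The plan's own figure: n = 2 × (118.5 × (1.960 + 0.842)/62)² = 57.4, so 58 per group, not 80. This mismatch is a separate matter and the present point does not rest on it.
- Standard error at 80 per group: 118.5 × √(2/80) = 18.74 mL. Power = Φ(62/18.74 − 1.96) = 91%.
- Assume a share f of the aPRP arm does not receive the product, gains nothing from allocation and stays in the analysis, with the SD unchanged. The difference becomes 62 × (1 − f).

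| Assumed f | Patients of 80 | Difference (mL) | Power |
|---|---|---|---|
| 5% | 4 | 58.9 | 88% |
| 10% | 8 | 55.8 | 85% |
| 20% | 16 | 49.6 | 75% |
| 30% | 24 | 43.4 | 64% |

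Every value of f here is an assumption.

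**The case against.** The strongest reply is that this is unpolished English in a condensed article and nothing more. Several parts of that reply stand.

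- A reader might infer that the arms receive different neutralising agents. No section assigns an agent to an arm, and both names occur in text about aPRP. They may be one agent rendered twice. Two names do not show different heparin status.
- A reader might infer that ANH blood is returned before neutralisation and aPRP after it. No section says so; it follows only from clause order under the first reading.
- A reader might infer that bleeding patients are denied aPRP. The bleeding clause has no conditional word, refers to the whole operation rather than the moment of return, and is a separate sentence from the one about the decision.
- A reader might infer that whole blood first meets citrate when bypass stops. The Discussion describes citrate being added in the collection of both products, at a 1:10 ratio by infusion pump.
- The decision sentence may mean only that the anesthesiologist carries out the procedure. The blinding section mentions more than one anesthesiologist, so the one deciding need not be the one kept blind.
- TEG is not the primary outcome.

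The full protocol may also set out the return steps. That would excuse omitted detail, but the difficulty here is text that is present and inconsistent. The last reading of the decision sentence is possible but not settled by the document, and as worded the sentence sits badly with random allocation and with an anesthesiologist who is not told it.

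**Conclusion.** The point holds as an inconsistency in how delivery of the randomised product is specified. The two subsections differ on the agent's name, the order of neutralisation and return, the product named, and whether bleeding status or a clinician's decision plays any part. The text therefore permits, without stating, a between-arm difference in the timing of return relative to neutralisation, and receipt of aPRP that is not determined by randomisation alone.

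The consequences are conditional. TEG at T3 and T4 is confounded only if return falls on different sides of neutralisation in the two arms. Drainage is affected only if some products are not returned. The documents give no frequency for that, and the dilution figures above show sensitivity under assumed shares, not an estimate. The stronger claims, that heparin status does differ by arm or that bleeding patients do not get the test product, are not supported. Severity is moderate: the harm is unproven, but the ambiguity concerns the intervention itself and is cheap to remove.

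**What to change.** Reconcile General anesthesia and aPRP collection into one return rule that covers both arms. It should use one agent name, state one order of neutralisation and return, name the product returned in each arm, and say once whether bleeding status or anesthesiologist discretion plays any role. What the rule says is for the clinical team. If discretion remains, state who exercises it and how that fits with the blinding described under Double-blind randomization and allocation concealment.

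Then:

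- define T3 and T4 relative to the same event in both arms, with the same wording in the Abstract, Study design {8} and Data collection and management;
- record the times of heparin neutralisation and of product return, and whether the product was returned, on the case report form;
- state that patients whose product was not returned are analysed in their randomised group, and that non-return is not a ground for removal under the non-adherence section.

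The cost is revised wording, two time stamps and one yes/no item per patient. By the protocol's own section on modifications {25}, the change needs ethics committee approval before it is implemented. Sample size and visits do not change.

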### Plans to promote participant retention and complete follow-up {18b}

No applicable. We believe that the focus of our experiment is on various markers during the perioperative phase. On the day of the procedure, the patient will be monitored until the patient is discharged from the PACU. We shall employ the same data collecting and statistical forms for all experimental data.

### Follow-up

Patients in this trial will be followed up by an investigator once a day on postoperative days 1–3 to record the drainage volume and the administration of IABP and ECMO.

### Data collection and management

Dedicated staff will record all data and complete a case report form for each patient. Relevant demographic characteristics and the patients’ past medical histories, including age, height, weight, and diagnosis, will be collected at the time of patient inclusion. Intraoperative data, including mean arterial pressure, heart rate, oxygen saturation, and central venous pressure, will be recorded before the beginning and after the end of collection and before and after the return infusion. TEG testing will also be performed before and after the collection and before and after the return infusion. The decision to use blood products such as fibrinogen, prothrombin complex, coagulation factors, and platelets will be made based on the TEG results.

### Determination of sample size

We calculate the required sample size based on the drainage volume (mean ± standard deviation) at 24 h after the end of the manual procedure. Our preliminary study showed that the drainage volumes at 24 h postoperatively in the aPRP and control groups were 316 ± 102 and 378 ± 133 mL, respectively. Eighty patients per group were therefore needed to detect a difference with a power of 80% and a type I error rate of 5% using the PASS software.

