### Statistical analysis

Statistical analysis will be carried out using the SPSS software, version 26.0 for Windows (SPSS, Inc., Chicago, IL, USA). Continuous variables will be described as mean (standard deviation) or median (25% and 75% percentiles) and analyzed using independent *t*-tests or Mann–Whitney *U* tests, respectively. Categorical variables will be described as a frequency or percentage and analyzed by *χ*^2^ tests. Prior to statistical analysis, each continuous variable will be analyzed to determine if it is normally distributed. If the assumption of a normal distribution is violated, the appropriate transformation will be used, and analysis using repeated measures analysis of covariance (ANCOVA) models may be more effective.

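### The sample size does not follow from its inputs: they need 59 per group for 80% power at 5%, and 80 per group gives about 91%

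*Protocol article*

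**What the plan says.** All of the sizing is in the protocol article, under Determination of sample size. The endpoint is drainage volume at 24 h. The preliminary study is reported as "drainage volumes at 24 h postoperatively in the aPRP and control groups were 316 ± 102 and 378 ± 133 mL, respectively". The operating characteristics are "a power of 80% and a type I error rate of 5% using the PASS software", and the conclusion is "Eighty patients per group were therefore needed to detect a difference with a power of 80% and a type I error rate of 5"%. The section does not state sidedness, a dropout allowance, a multiplicity adjustment or any other inflation.

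The abstract (Methods and analysis) confirms the total and the allocation: "160 patients randomized 1:1 to receive aPRP (test group) or autologous whole blood". It also places drainage at 24, 48 and 72 h under the primary objective. Statistical analysis names the test: "Continuous variables will be described as mean (standard deviation) or median (25% and 75% percentiles) and analyzed using independent" t-tests, or Mann–Whitney *U* tests for variables reported as medians.

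**The concern.** The section prints every numerical input and presents 80 per group as their direct consequence, so the calculation can be repeated, and it does not come out at 80. Either the stated power is about 11 percentage points too low for this sample size, or the alpha, power or inflation used in the software was not the one printed.

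The explanation matters because the document makes several candidates consequential:

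- **Attrition.** The article provides for removing patients after enrolment. Post-operative deaths are listed among the exclusion criteria (Inclusion and exclusion criteria), cases whose collected blood is needed for extracorporeal circulation are excluded (General anesthesia), and clear protocol violators are left out of the results (The treatment of non-adherence and missing data). If 80 analysed patients per group were really needed, every such loss takes power below 80%. If 59 are enough, up to 21 per group can be lost first.
- **Multiplicity.** Three drainage times sit under the primary objective, but the sizing uses one of them at 5%. A three-way split of alpha would roughly produce 80, but then the stated 5% is not the level used.

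The 62 mL difference on which the trial is implicitly sized is also not the difference that 80 per group detects with 80% power.

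**Working it through.** **Inputs**

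- Means 316 and 378 mL, so the difference is 378 − 316 = 62 mL (Determination of sample size).
- SDs 102 and 133 mL (same section): 102² + 133² = 10,404 + 17,689 = 28,093. The root-mean-square SD is √(28,093/2) = 118.5 mL, and the standardised difference is 62/118.5 = 0.523.
- Type I error 5%, power 80% (same section).
- Allocation 1:1, 160 in total (abstract).
- Two-sided testing is my assumption, because sidedness is not stated. One-sided is tried below.

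**Attempt to reproduce 80 per group**

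Normal approximation, n per group = (SD₁² + SD₂²)(z₀.₉₇₅ + z₀.₈₀)² / Δ²:

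28,093 × (1.96 + 0.8416)² / 62² = 57.4, so 58 per group.

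Noncentral *t* with unequal variances (Welch), two-sided 5%:

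| n per group | Power |
|---|---|
| 58 | 79.7% |
| 59 | 80.4% |
| 80 | 90.8% |

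The requirement is 59 per group, or 118 in total; the pooled *t*-test also gives 59. Since 160/118 = 1.36, the plan enrols 36% more than its inputs need. The normal approximation agrees on power at 80: 62/√(28,093/80) − 1.96 = 3.31 − 1.96 = 1.35, which is 91.1%.

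**Difference detectable with 80% power at 80 per group**

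(1.96 + 0.8416) × 118.5 × √(2/80) = 52.5 mL by the normal approximation, 52.8 mL by noncentral *t*. The inputs imply 62 mL.

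**Other readings that keep 80% power and 5% alpha**

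| Reading | n per group |
|---|---|
| One-sided 5% | 46 |
| SD 133 in both arms, two-sided | 74 |
| Mann–Whitney, efficiency 0.955 | 59/0.955, so 62 |
| Mann–Whitney, worst-case efficiency 0.864 | 59/0.864, so 69 |

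None reaches 80. By the normal approximation, a common SD of about 140 mL would be needed, which is above both reported SDs.

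**Readings that come near 80 by using an input the text does not state**

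| Reading | n per group |
|---|---|
| 90% power, two-sided 5% | 78 (normal: 77) |
| 80% power, two-sided alpha 0.05/3 = 0.0167 | 79 by Welch; n = 80 gives 81.1% |
| 95% power, one-sided 5% | 80 |
| 59 inflated for 26% dropout | 59/0.74 = 79.7, so 80 |

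A 20% dropout allowance would give only 59/0.80 = 73.75, so 74.

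**The case against.** The strongest reply is that the discrepancy is conservative. On its own inputs the trial is larger than required, and nothing about its conduct depends on the sentence. That is true, and it is why the point calls for a correction and not a new sample size.

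Second, 90.8% is a ceiling. It assumes that all 160 patients are analysed with a *t*-test on roughly normal data. If, for illustration, 20% were lost (64 per group analysed), power would be 83.5%. With a Mann–Whitney test on all 80 per group it would be about 89%, or about 86% in the worst case. This stands: the 91% should be labelled as complete-data power. None of these figures brings power down to the stated 80%.

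Third, the article never names a smallest detectable difference. That is also true. The 62 mL is implied by the means and is not declared as a target, so the 53 mL figure only illustrates the discrepancy.

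Fourth, this is a condensed article, and a fuller protocol may hold a dropout allowance. Leaving one out would be no fault in itself. But the article derives 80 directly from the printed inputs, and an allowance recorded elsewhere does not make that inference correct.

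Finally, a three-way alpha split is only one candidate. A 90% power target (78, rounded up to 80) is at least as simple. The document supports neither.

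**Conclusion.** The concern holds. The stated sample size cannot be reproduced from the stated inputs: they need 59 per group, not 80, and 80 per group gives about 91% power with complete data, not 80%. The result assumes a two-sided test and the printed SDs. Relaxing either assumption (one-sided, or the larger SD in both arms) still gives fewer than 80. The trial is not underpowered on its inputs. What is wrong is the stated power, or else the stated alpha, or an inflation step has been left out. The document does not show which.

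**What to change.** Keep 160 and correct the sentence under Determination of sample size so that it gives the inputs actually entered in the software: test, sidedness, alpha, power and any inflation.

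- If the printed inputs are right: with complete data, 80 per group gives 91% power at two-sided 5% for a 62 mL difference (SDs 102 and 133 mL). Power stays at 80% or more while at least 59 per group contribute 24 h drainage, that is, with up to 21 per group giving no data. This margin should be called planned attrition only if it was planned.
- If alpha was split over the three drainage times: state two-sided alpha 0.0167 and 81% power.
- If the target was 90%: state 90% power, 78 per group, rounded up to 80.

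The cost is one sentence. Enrolment does not change.
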